### Study Procedures

#### Recruitment

Potentially eligible patients, identified from clinical databases, will be contacted by a member of the research team and invited to attend an information event or specialist research recruitment clinic. The information event will be held locally on a Saturday or in the evening to make the event more convenient for patients and their carers. The event will allow patients to meet the research team, have an educational talk, and find out about the study. They will also be able to look at the devices and iPad app as well as ask any questions. Patients interested in participating in the study will be given a participant information sheet (PIS) and invited to come to a research clinic for screening and enrollment.

At the research clinic, patients will be reviewed by a clinical research fellow and screened for suitability for the study by the research team. Patients and carers will be able to view and try out the self-monitoring devices and tablet-based IT system. Capacity to operate these systems will be assessed as part of screening using a checklist, assessing the patient/carer confidence in using the devices and ability to perform the measurements. Those who meet eligibility criteria will be given a PIS and a carer information sheet if necessary. After adequate time to read, understand, and ask questions (at least 24 hours), patients will be invited back to the research clinic to give informed consent. Baseline data will be captured on paper case report forms (CRFs) and uploaded to a local study database, separate from the self-monitoring database held by Aseptika.

#### Participant and Carer Training

Volunteers will be trained by a research nurse and Aseptika personnel during a visit to the participant’s home. A home visit will clarify which 3G cellular network is available in their location (for Internet access) and will ensure that the participant has space to install a small dedicated freezer and that there is access for delivery.

Each participant will be provided with the following items and participant and carer will be trained on their use:

Physical activity tracker: this will be set up for them and they will be shown how and when to wear it.Smart scale: the participant will be instructed how to weigh themselves and how this measures their body composition (they will be instructed to perform this in bare feet).Blood pressure cuff: the participant will be instructed how to take their own blood pressure and what the results mean.Pulse oximeter: the use of a pulse oximeter and how it works will be explained.Thermometer: the participant will be provided with a noncontact infrared thermometer and will be shown how to take their temperature.Peak flow meter: participants will be shown by the research nurse how to measure their peak flow and FEV_1_ using a simple, automated device.Sputum and urine samples: participant will be taught how and when to take a sample and how to store the sample in the containers provided in the freezer that will be supplied.iPad mini and questionnaires: participant will be trained on how to charge the iPad mini, how to switch it on and off, etc. A short questionnaire about symptoms, medications, and health care usage will be completed on the iPad mini using colorful self-explanatory series of screens within the Activ8rlives App. The display will be brightly colored, and any text (which will be kept to a minimum) will be large in size.

Participants will be able to use the iPad mini for personal use as well as for daily study use within the limits specified and agreed to in the participant consent form. Participants will be requested to take this equipment with them to the hospital if they are admitted and to continue recording these data in the hospital. Initial training will take approximately 60 minutes.

Following training, questions about use of the equipment will be answered by the research nurse and referred to the company in the event of technical difficulties with the IT system. The iPads will be supplied preconfigured with all software installed and an account for the volunteer already created and defined. A remote access technical support solution will also be preinstalled allowing the company to remotely access the iPad to resolve problems in the event of significant failures. If required, follow-up visits to the participants will be undertaken. Every effort will be made to ensure that the volunteer is adequately trained and supported for the duration of the study.

#### Study Assessments

Participants will be asked to undertake the following once a day every day during a 6-month follow-up period, with assistance from carers as appropriate. Figure 1 illustrates the equipment that will be provided to the participant to facilitate these assessments.

**Figure 1 figure1:**
[figure not shown]
Equipment provided to participant to complete the assessments.

Each participant will be provided with a 3G-enabled tablet (iPad) and will upload peak flow, FEV_1_, pulse rate, oxygen saturation, blood pressure, temperature, and physical activity data on a daily basis. The participants will be provided with a set of instructions about uploading the data onto the iPad. The participants will be blind to their continuous data over the duration of the study but will see the values generated daily on the screens of the devices. There will be no requirement for the participant to enter numerical values into the software as all monitoring devices connect directly reducing the risk of inaccurate data entry. The data collected on the iPad is automatically transmitted to the Cloud databases. No information is stored on the iPad and if the iPad is lost, there is no risk that these data could be accessed. The company is able to track the iPad’s location in the event that it is stolen or lost.

The information uploaded by the volunteers will be remotely reviewed daily by Aseptika’s Directors to ensure that data has been uploaded on a daily basis and there are no technical problems. Technical problems will be remedied remotely by the Aseptika technical staff. In the case of information not being uploaded, Aseptika’s investigator will initially inform the research nurse who will contact the volunteer by telephone to enquire if there have been any difficulties. Should any volunteers find the technology difficult to manage, they will be offered a further home visit for instructions and training.

#### Sample Production and Home Storage for Sputum and Urine Samples

Containers will be prelabeled with the participant study number, expected contents (sputum or urine), and the day and date.Participants will be asked to fill the supplied pot with sputum and ensure the lid is correctly sealed.Participants will be asked to collect urine in the bulk container and secure the lid.They will then connect the Vacutainer to the cap of the urine container (as per supplied instructions), and the Vacutainer will begin to fill with urine.Bulk urine collection pot is to be discarded.Store both containers in sputum and urine collection bags inside of the supplied –20°C freezer.After 1 month, these will be transferred for bulk storage at the Queen Alexandra Hospital in a designated –70°C freezer and a new batch of containers will be provided.

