**Methods:**

We plan to recruit 30 adult participants with COPD or non-CF bronchiectasis who have cultured *P aeruginosa* or *H influenzae* during an exacerbation in the last 6 months. They must produce sputum on most days and should have been stable for 4 weeks prior to entry. Daily data collected will include symptoms, health care usage, medication, weight, FEV1, physical activity level, blood pressure, oxygen saturation, and temperature. Sputum and urine samples will be provided daily. These data will be analyzed to assess predictive value in detecting upcoming exacerbations. Qualitative data will be gathered through self-administered questionnaires and semistructured interviews to gather information on participant coping and their use of the technology involved.

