### Assessment of Safety

This is a noninterventional study and is therefore considered to be of no additional safety risk compared with usual clinical practice. All patients are expected to have a number of comorbidities and on-going symptoms due to their illness. All study procedures in use are the usual standard of care for this population and are not novel. The test used to observe the variation in levels of Exotoxin A is a new test but one that is validated and in itself provides no risk of harm to the participants; it is not performed on the participants themselves but on their sputum, which they would ordinarily be producing daily, and it will not change any clinical treatment as the results will not be available to the participant or their clinical team.

There is therefore no clear rationale for additional safety monitoring during the study period or for the expedited reporting of any serious adverse events. However, as study procedures are being conducted more frequently by the patients in their homes (as part of their daily routine), there may be an increased frequency of expected side effects or adverse events for some patients. The most likely adverse event during procedures is an increased risk of fainting for those participants who are susceptible to fainting during spirometry (specifically daily peak flow, which requires blowing rapidly and forcefully into a spirometer). Therefore, the following risk-adapted safety monitoring procedures are to be followed during the study period.

Participants will be asked to report any of the expected adverse events (dizziness or light-headedness and fainting) to the research team if they occur at a level which causes significant discomfort to the participant so that the research team can provide any further training or adjustments to the way in which the measurements are taken or reduce the frequency at which the participant is to take the measurement.

The chief investigator and study team will record and monitor any adverse events caused due to the increased frequency of the self-monitoring assessments. If there is any concern over these events or if they become unacceptable and in any circumstance cause the risk-to-benefit ratio to tip, they should be expedited to the sponsor and may be subsequently reviewed by the Research Quality Committee.

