#### Analysis of Endpoints

The first stage of the data analysis is to use data on the collected parameters (eg, peak flow, pulse rate, oxygen saturation, activity data) to predict when an exacerbation is likely. Control charts will be used to determine the boundaries of normal behavior for each parameter. Separate control charts will be used for each participant, as what constitutes normal behavior will vary from participant to participant. When a parameter strays from normal behavior (eg, exceeds 99% control limits), an exacerbation will be predicted.

To examine the association between predicted exacerbation and actual exacerbation, participant follow-up will be divided into periods of time (eg, 7-10 days). A comparison of actual exacerbation when exacerbation has and has not been predicted will be made. To allow for the repeat measurements over time from the same participants, the analysis will be performed using multilevel logistic regression. Additionally, the sensitivity and positive predictive value of the predictions will also be calculated. Estimated values will be presented along with corresponding confidence intervals. Further exploratory analysis using novel computing methods will be conducted.

Health care use data will be presented descriptively (eg, the frequency and type of health care contacts over the study period for different participant groups).

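### Time at −20°C is tied to position in each monthly sputum batch, so a material storage loss could move biomarker alarms from early to late in the batch; adjusting for days at −20°C is a cheap safeguard

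*Protocol article*

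**What the plan says.** The Abstract (Methods) states "Sputum and urine samples will be provided daily", and Study Assessments asks for this "once a day every day during a 6-month follow-up period". Sample Production and Home Storage for Sputum and Urine Samples gives the storage steps: "Store both containers in sputum and urine collection bags inside of the supplied –20°C freezer", then "After 1 month, these will be transferred for bulk storage at the Queen Alexandra Hospital in a designated" freezer at −70°C, when a new set of pots is issued. The same section states "Containers will be prelabeled with the participant study number, expected contents (sputum or urine), and the day and date". It does not say that the transfer date is recorded.

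The Primary Objective builds individual prediction models from longitudinal sputum biomarkers, telemetry and symptoms. Sampling and Sample Size takes the sputum biomarkers as the predictor. Analysis of Endpoints states "Control charts will be used to determine the boundaries of normal behavior for each parameter", with a separate chart for each participant and 99% limits as an example. It does not say how the limits are estimated and mentions no term for storage time. Assessment of Safety says "The test used to observe the variation in levels of Exotoxin A is a new test but one that is validated" and gives no stability figure.

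**The concern.** The charts compare a participant's value today with that participant's own other days. They are therefore exposed to any artefact that is ordered in time within a person. Time at −20°C is such a variable: the storage schedule fixes it completely by position in the monthly batch.

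If a biomarker decays at −20°C, the oldest samples in a batch read low and the newest read nearly true. The series then climbs through each month and drops after each transfer. A climb is the pattern the study is looking for. The same true rise could be flagged or missed according to how close it falls to the next collection. Comparing participants would not reveal this, because all follow the same cycle.

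**Working it through.** **The plan's own figure.** The sample size reproduces. A two-sided, continuity-corrected comparison of 60% with 10% at a 1:11 ratio, 5% significance and 90% power gives 10 + 110 = 120 periods. The design effect is 1 + 11 × 0.18 = 2.98, so 120 × 2.98 = 357.6, about 360, and 360/12 = 30 participants. The storage point does not alter this calculation.

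**Storage time.** In a 30-day batch, days at −20°C are 29, 28, …, 0, with mean 14.5 and SD 8.66, repeated about 180/30 = 6 times.

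**Assumptions, none given in the document.** Log level = independent normal noise with SD σ, minus k × (days at −20°C). No true exacerbations. Loss over 29 days is 1 − exp(−29k): 13.5%, 25.2% and 44.0% for k = 0.005, 0.01 and 0.02. Limits use the participant's own mean and SD over 180 days, with the upper limit at z = 2.576.

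**False upward alarms** (simulated; % of stable 10-day periods by third of the batch; the total is the mean of the three):

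| σ | Loss per day | First | Middle | Last | Total |
|---|---|---|---|---|---|
| 0.3 | 0 | 4.6 | 4.6 | 4.8 | 4.7 |
| 0.3 | 0.5% | 2.5 | 4.3 | 7.1 | 4.6 |
| 0.3 | 1% | 1.3 | 3.6 | 9.0 | 4.6 |
| 0.3 | 2% | 0.2 | 1.6 | 10.5 | 4.1 |
| 0.5 | 1% | 2.2 | 4.3 | 7.4 | 4.6 |
| 1.0 | 0.5% | 3.8 | 4.8 | 5.1 | 4.6 |
| 1.0 | 1% | 3.4 | 4.6 | 5.9 | 4.6 |

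The total does not rise. The alarms change place.

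**Sensitivity.** The sawtooth inflates the fitted SD by r = √(1 + (8.66k/σ)²). At σ = 0.3 this is 1.010, 1.041 and 1.155 for 0.5%, 1% and 2% per day. A true rise of 2.5 SD on a sample stored s days is flagged with probability 1 − Φ(2.576r − 2.5 + k(s − 14.5)/σ).

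- No loss: 1 − Φ(0.076) = 47%.
- 1% per day, taking the centre of each third (s = 24.5, 14.5, 4.5): 1 − Φ(0.514) = 30%, 1 − Φ(0.181) = 43%, 1 − Φ(−0.152) = 56%, mean 43%. Simulation gives 31% early, 56% late and 44% on average.
- 2% per day: 1 − Φ(1.141) = 13%, 1 − Φ(0.474) = 32%, 1 − Φ(−0.193) = 58%, mean 34%.

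**Other ways to set limits** (two-sided daily false-signal rate):

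| Scenario | Overall SD | Moving range | 14-day baseline |
|---|---|---|---|
| No loss, σ = 0.2 | 0.95% | 0.98% | 2.7% |
| 30% lost over the longest stay, σ = 0.2 | 0.89% | 1.97% | 5.5% |
| 50% lost, σ = 0.5 | 0.92% | 1.56% | 4.5% |
| 10% lost, σ = 0.5 | 0.94% | 1.01% | 2.8% |

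Only with moving-range or short-baseline limits does the total rise.

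**Can the study measure the slope?** With 20 *P aeruginosa* participants, 180 samples each and σ = 0.3, the standard error is 0.3/√(20 × 180 × 8.66²) = 0.00058, about 0.06% per day. In simulation, adjusting for a pooled slope restored about 4.5% to 4.8% in every third at every loss rate, and changed nothing material at zero loss.

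**The case against.** A reader might infer that any storage loss will be read by the charts as change, that it will generate extra false alarms, and that it will lower the positive predictive value. The document does not support this. It shows no loss and gives neither the loss rate, the within-person SD nor the limit method. A 10% loss hardly moves the overall signal rate under any limit type tried. With overall-SD limits the total of false alarms is flat or falls. The alarm simulation contains no exacerbations, so it yields no positive predictive value.

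It is also fair to say that stability data and sample handling usually sit in a laboratory manual or full protocol, and a covariate adjustment in the analysis plan. Their absence from an article is not an error, and the assay is described as validated. The example parameters in Analysis of Endpoints are telemetry, which freezer time cannot affect. Independent daily noise is a simplification, and autocorrelation would change the rates.

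These points limit the size of the concern. They do not remove the structure: the storage schedule is stated, it ties storage time to position in the batch, and the biomarker series is used within person. A validated assay does not by itself tell us that 30 days at −20°C was covered.

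**Conclusion.** The point holds as a conditional one, for sputum biomarkers only. Storage time at −20°C is fully tied to position in the monthly batch. If loss is material relative to day-to-day variation, alarms shift from early to late in the batch and sensitivity falls early in it. With overall-SD limits, σ = 0.3 and 1% loss per day, the late third alarms about seven times as often as the early third (9.0/1.3 = 6.9), with no rise in the total. Average sensitivity falls only slightly there (47% to 44%) and more at 2% per day. At σ = 1.0 and 0.5% per day the effect is negligible. With moving-range or short-baseline limits the total would also rise. These are scenarios under assumed values, not estimates for this study. The matter is a cheap improvement to the analysis, not a demonstrated fault in it.

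**What to change.** For each sputum biomarker:

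1. Record the transfer date of every batch. Derive days at −20°C as transfer date minus the date on the pot label.
2. Regress the log biomarker on days at −20°C, with a separate mean for each participant and one slope pooled over participants, using days outside exacerbations. Report the slope with its confidence interval.
3. Set the control limits on values adjusted for that slope, and give the unadjusted charts as a sensitivity analysis.
4. Cite stability data for up to 30 days at −20°C if they exist.

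The cost is one derived variable and the assumption that the slope is common to all participants. No extra samples or visits are needed. The Results section says the study is already in data analysis; the adjustment remains possible at that stage if transfer dates were kept or can be recovered.

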#### Clinic Visits

Participants will be required to attend the clinic for a follow-up visit at months 3 and 6 (study completion) ± 2 weeks. Participants will attend their normal review with the medical team that usually involves lung function, sputum sample for culture, and clinical review. They will then have a research visit which will involve disease-specific control and quality of life questionnaires (Quality of Life–Bronchiectasis, Short Form Health Survey, St. George's Respiratory Questionnaire, EuroQol 5-Dimension Questionnaire) as well as noting any changes to treatment and exacerbations. The data collected from these visits will be recorded on paper CRFs which will then be uploaded by a member of the research team to a local study database with restricted access.

#### Health Economics

In preparation for a future cost-effectiveness trial of the self-management system, a questionnaire to collect health care use data will be piloted to capture resource use. These data will be analyzed descriptively. The daily questionnaire within the Activ8rlives app asks if participants have been in contact with a health professional or been in hospital in the last 24 hours. If they answer yes, they will be prompted to give more information about who they saw and for what reason. This will capture data on the participants’ health care use for their respiratory condition as well as other conditions.

#### Qualitative Methods

Qualitative methodology will be used to explore the psychosocial questions: How do the participant and main carer experience self-managing their condition under routine care? What is the participant’s expectation of taking part in the study? How does the participant experience collecting daily self-monitoring data and using the devices provided? Qualitative research seeks to describe, understand, and explain a particular phenomenon to make explicit the experiences and perceptions of the research subjects [8,9]. This is achieved by exploring the data (usually words) for conceptual definitions on how people perceive situations to provide explanations of why something happens in a particular way as well as looking for typologies or classifications of grouping of people (or situations) that tend to have common characteristics, opinions, and experience. Qualitative data will be collected at the end of the study (6 months) through face-to-face semistructured interviews with participants or paired interviews with carers, based on participant preference. Carers will not be interviewed separately.

All interviews will be guided by a semistructured topic guide although free discussion of experiences and ideas will also be encouraged. The semistructured interviews will be audiotaped and field notes taken to describe context, interview process, and initial theme development. A choice of venue, either at home or suitable hospital room, will be used. All qualitative interviews will be conducted by the same trained research fellow supported and supervised by another experienced qualitative researcher.

It is anticipated that the semistructured face-to-face interviews will take between 45 minutes to 1 hour to complete, depending on what the participant wishes to share. The interview will be terminated at any point the participant wishes to stop and this will not influence their subsequent treatment. As a small token of appreciation for time given to take part in the interviews, each participant will be offered a £10 (US $13) gift voucher on completion.

The interviews will be digitally recorded, transcribed verbatim, and entered into NVivo 10 (QSR International), a qualitative software package for systematic and transparent data management. All participant names will be removed from the transcripts to retain confidentiality. Care will be taken to always ensure any direct quotes used in study reports or papers to illustrate the findings will not be directly attributable to individuals.

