## Methods

### Overview

In a mixed methods study, a longitudinal cohort of participants and their carers (where appropriate) will be asked to collect physiological, biological, and disease outcome data over a 6-month period. Neither participants nor the clinicians responsible for participant care will have access to the longitudinal data, and this information will not be used to make clinical decisions. The laboratory samples will be analyzed in a blinded manner. These data will then be analyzed to develop a model for predicting onset of exacerbations that can be built into a self-monitoring system.

Qualitative methods will be used to explore participant and carer experiences of using the technology and performing daily self-monitoring assessments. The expected duration of participation in the cohort will be 6 months, with an invitation to complete a self-administered questionnaire at baseline to inform a face-to-face semistructured interview with patients with or without carer joint participation at the end of the follow-up period.

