### Sampling and Sample Size

Using the sputum biomarkers to predict exacerbations, we based the sample size on the difference in exacerbation frequency in time periods when an exacerbation was predicted compared to time periods when no exacerbation was predicted. This will give an odds ratio of exacerbation following detection of sputum biomarkers.

Time periods will consist of approximately 10 days, of which it will be estimated that there may be on average 12 per participant (assuming an average of 4 months of follow-up). It is estimated that an exacerbation will occur in 60% of time periods in which it is predicted and 10% of time periods in which it is not predicted. It is also assumed that a predicted exacerbation will be made in only 1 in 12 time points (8% of all time points). Using a 5% significance level and 90% power, it is calculated a total of 120 time periods will be required.

However, as there are multiple time periods from the same participant, the data values are unlikely to be independent of each other and thus the sample size requires inflating. Assuming intraclass correlation of 0.18, a design effect of approximately 3 is calculated. This implies that 360 time periods are required for the analysis. This equates to a total of 30 participants for the study. The proposed 30 participants will consist of 20 participants with chronic *P aeruginosa* infection (10 with primarily COPD and 10 with NCFB) and 10 participants with *H influenzae* infection.

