#### Self-Administered Questionnaire

After consent and on entry to the main study, all patients but not carers will be asked to complete a self-administered questionnaire (to be developed with advice from the Patient Public Involvement [PPI] team members) with open and closed questions regarding self-awareness/perception of burden of disease, self-management including use of medication, identifying signs and symptoms of deterioration, problem-solving, seeking support/health care professional input during usual care as well as rationale and expectation of participation in the study and perceived barriers and enablers to successful completion in the study. We anticipate that this short self-administered questionnaire will take approximately 30 minutes to complete. The purpose of this self-administered questionnaire is to use individual responses to act as an “aide memoire” at the follow-up interviews.

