#### Discontinuation or Withdrawal of Participants From Study

Participants not complying with study requirements or failing to upload data or collect a sample will be retrained. Significant nonadherence (eg, noncollection of data and samples for a period of several weeks) may lead to withdrawal of the participant from the study by the study team. If participants and carers are not willing to continue data collection, they may decide to withdraw from the study and will be requested to return all the equipment.

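### The only interview is fixed at 6 months with no stated route for participants who withdraw, so the interview evidence on acceptability is likely to over-represent those who tolerated daily monitoring

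*Protocol article*

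**What the plan says.** **Timing of the interview.** The Overview of the Methods describes a "face-to-face semistructured interview with patients with or without carer joint participation at the end of the follow-up period". Qualitative Methods repeats the timing: "Qualitative data will be collected at the end of the study (6 months) through face-to-face semistructured interviews with participants". Neither section gives a second time point. The planned period is the full half-year: "The expected duration of participation in the cohort will be 6 months".

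**Leaving the study.** The section on discontinuation and withdrawal gives two ways out. Lasting non-collection "may lead to withdrawal of the participant from the study by the study team". Participants and carers who no longer wish to collect data are covered by the other: "they may decide to withdraw from the study and will be requested to return all the equipment". The section does not mention the interview.

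**What the interview is for.** The Secondary Objectives include exploring whether the platform is feasible and acceptable for daily use. Qualitative Methods asks how participants experience the devices and the daily data collection.

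**Other contacts.** A questionnaire is completed at entry, and its stated purpose is to "use individual responses to act as an “aide memoire” at the follow-up interviews". When uploads stop, the research nurse "will contact the volunteer by telephone to enquire if there have been any difficulties". The month 3 clinic visit collects disease-control and quality-of-life questionnaires, treatment changes and exacerbations. Adherence to data input is a separate secondary objective, and the analysis population is everyone recruited.

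**The concern.** Acceptability is a judgement by users. The people most likely to judge the system unacceptable are also the most likely to stop using it, and unwillingness to continue is one of the article's own grounds for withdrawal. The section on benefits and burdens accepts that the daily work may weigh heavily on people who already have demanding treatment. If the only interview comes after six months, the views of those who stopped can drop out of the evidence. The direction of the resulting bias is predictable: the system looks more acceptable than it was to all who tried it.

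Two later uses depend on this evidence. The Discussion wants to reduce the monitoring load in future, and the rationale section foresees a large randomised trial of the system. Both need to know why people stopped. The carer's account is exposed in the same way, because carers are interviewed only jointly with the participant.

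**Working it through.** **Step 1. The timing and exit rules side by side.** The interview belongs to the end of follow-up, at 6 months. Withdrawal is from the study as a whole, and the one action attached to it is return of equipment. A participant who leaves at, say, month 2 has no interview scheduled at exit, and the text does not say that an invitation follows at month 6.

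**Step 2. Whether another stated source records a leaver's experience of the devices.**

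| Source | When | What it gives for a leaver |
|---|---|---|
| Entry questionnaire | Before device use | Expectations and perceived barriers, not experience; meant as a prompt for the later interview |
| Nurse telephone call | After missed uploads | Troubleshooting; not described as recorded data or as part of the framework analysis |
| Month 3 visit | If still in the study | Health status, treatment and exacerbations; nothing on the devices |
| Adherence rates | Throughout | That input stopped, not why |

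The interview is therefore the only stated source on how the devices and daily collection were experienced. Feasibility is different: adherence counts inform it directly and include non-completers.

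**Step 3. Whether the sample size tells us how many leave.** The planning text is "assuming an average of 4 months of follow-up".

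- Its own figures reproduce. Comparing 60% with 10% at a 1:11 ratio, with two-sided 5% significance, 90% power and a continuity correction, needs 10 + 110 = 120 periods.
- The design effect is 1 + (12 − 1) × 0.18 = 2.98, about 3.
- 120 × 3 = 360 periods, and 360 / 12 = 30 participants.

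No figure here is in dispute. To go from a 4-month average to a number of leavers, assume that the whole shortfall from 6 months is early withdrawal and that leavers stay t months on average. Then 6(1 − w) + t·w = 4, so the share leaving is w = 2 / (6 − t).

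| t (months, assumed) | w | Leavers of 30 | Completers of 30 |
|---|---|---|---|
| 0 | 0.33 | 10 | 20 |
| 1 | 0.40 | 12 | 18 |
| 2 | 0.50 | 15 | 15 |
| 3 | 0.67 | 20 | 10 |

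If the shortfall is instead missed days among people who stay, the number of leavers could be close to 0. The article does not say which applies, so the 4-month figure does not fix the number of leavers.

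**The case against.** The strongest reply is that this is an inference from silence in a condensed article. No sentence excludes withdrawn participants from the interview. The definition of the end of study lists the last data upload and the last interview as separate events, so the interview is not tied to continued uploading. A leaver could be invited at month 6, and exit arrangements may stand in a full protocol that is not shown.

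That reply defeats three stronger readings that a reader might infer:

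- **That leavers are never interviewed and completers alone answer the objective.** The text supports only that no route is stated.
- **That everyone who finds the system too burdensome leaves first.** The first response to non-compliance is retraining. A further home visit is offered to those who struggle with the technology, and withdrawal by the study team is only a possibility. Burdened participants may stay and be interviewed.
- **That 12 or 20 of 30 will leave.** These figures need an assumed cause and an assumed leaving time, and the Results section's favourable account of uploading does not suggest heavy early loss, although it gives no withdrawal count.

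It is also fair that feasibility has other evidence, that the objective is secondary and exploratory, and that recruitment is complete and the study is in analysis.

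The reply does not remove the point that remains. The interview time is stated twice, not left open, and the stated time is a poor one for people who stop early. None of the other contacts records their experience.

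**Conclusion.** The concern holds in a limited form. The article fixes the only interview at the end of follow-up and states no route to it for those who withdraw or are withdrawn. Followed as written, the interview evidence on acceptability is likely to over-represent people who tolerated daily monitoring, with bias towards a favourable finding. This rests on one assumption: that unwillingness to continue is related to how acceptable the system was found. The article's own ground for withdrawal makes that plausible.

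The size cannot be derived from the document. The table above is an illustration, not an estimate. With 30 participants, each leaver not interviewed is 1/30, or 3.3%, of the sample. The primary objective is unaffected, and feasibility is only partly affected. The change is worth making because it is cheap, not because the loss is known to be large.

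**What to change.** In Qualitative Methods and in the section on discontinuation and withdrawal, set the interview at month 6 or at withdrawal, whichever is earlier. Offer it to every withdrawing participant, whether the decision was theirs or the study team's, with a short telephone version for those who do not want a meeting. Record the reason for stopping where the participant gives one. Report the acceptability findings with the number of leavers interviewed and the number not interviewed.

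If the interviews are already complete, the timing can no longer change. In that case report the same counts, with reasons for stopping where known, and limit the acceptability conclusion to those interviewed.

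The cost is new wording in two sections and an amendment, whose class depends on the ethics committee's definitions. There is still at most one interview per participant, by the same research fellow with the same topic guide, and home interviews are already allowed. The telephone option departs from the face-to-face format and would need stating. The downside is small: some leavers will decline, and interview times will vary.
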